### Statistical considerations

#### Sample size

The target sample size of 50 patients will allow estimation of the prevalence of OPM, AE rate and the impact on treatment plans with 95% CI bounds not exceeding 10% if the OPM prevalence is ≤15%. This represents a change in estimated prevalence, which was initially set at 70% (requiring a minimum sample size of 96). The initial OPM estimate of 70% reflected solely the retrospective data previously reported.^3 4^ The updated estimate of OPM prevalence and sample size calculation acknowledges data from the first 12 recruits to STRATIFY, of whom only one case of OPM has been observed (8.3% OPM rate).^19^ The reduction in the sample size from 96 to 50 cases means the trial will no longer have adequate power (80%) to detect an OS HR of 0.5 as planned in previous iterations of this protocol. This original HR corresponded to data from previous retrospective studies, which reported a median OS in OPM positive 6.32 months vs 12.65 months in OPM negative cases.^4^ OS differences between OPM positive and OPM negative groups will nevertheless be reported. Post hoc power calculations taking account of the observed prevalence will be performed.

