### Pleural staging by thoracoscopy

VATS thoracoscopy under GA is likely to be a highly sensitive staging tool for mini-PE.^11^ In previous studies it has also been combined with pleural lavage cytology (PLC, which involves saline irrigation during surgery in patients without an effusion).^12 13^ However, VATS is not a practical option for all patients, in whom non-surgical treatments are frequently required due to comorbidities or patient choice. In addition, the significance of PLC results is not clear, since positive results might not necessarily preclude surgical resection.^12^ By contrast, LAT is the gold-standard diagnostic test for patients with larger, symptomatic effusions and offers diagnostic performance to equivalent to VATS (sensitivity 93% (95% CI 91% to 94%)) and a low major complication rate (2.3% (95% CI 1.9% to 2.8%).^14^ LAT can be performed as a day-case in patients with mini-PE/no PE, but its performance and safety profile may differ in mini-PE, and this has never been prospectively evaluated. Staging by Thoracoscopy in potentially radically treatable Lung Cancer associated with Minimal Pleural Effusion (STRATIFY) will determine the true prevalence of OPM using either LAT or VATS, with sites encouraged to offer LAT when it is technically feasible. This will be assessed at a dedicated screening visit when LAT is the method preferred by the local team.

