#### Statistical analysis plan

##### Primary efficacy analysis

The estimate of the proportion of cases demonstrating OPM (OPM positive) and the associated 95% CI will use standard statistical methods. The CI will be based on the Clopper-Pearson exact approach.

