##### Secondary efficacy analyses

The estimate of the proportions of OPM demonstrated/not demonstrated and LAT complete/LAT incomplete and the associated 95% CIs will use standard statistical methods. The CI will be based on the Clopper-Pearson exact approach. The comparison of the RFS and OS between OPM positive and OPM negative patients will be illustrated with Kaplan-Meier curves; the HR will be estimated using Cox regression. AE data and the impact on oncological treatment plans will be summarised in tables and listings.

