##### Safety analysis

AE data will be summarised in tables and listings.

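### The ±10-point precision promised for the adverse event rate and treatment-plan impact is tied to OPM prevalence, which does not determine it; at n=50 it holds only if those proportions are themselves low (or very high).

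*Protocol article*

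**What the plan says.** The Sample size section opens with "The target sample size of 50 patients" and says that this number "will allow estimation of the prevalence of OPM, AE rate and the impact on treatment plans with 95% CI bounds not exceeding 10" per cent. The only condition attached is "if the OPM prevalence is ≤15" per cent. One sentence thus covers three quantities: OPM prevalence, the AE rate and the impact on treatment plans. No expected AE rate and no expected proportion of changed plans is given.

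The analysis sections treat the three differently. For the primary endpoint, "The CI will be based on the Clopper-Pearson exact approach". Under Secondary efficacy analyses, intervals are named for two proportions: "The estimate of the proportions of OPM demonstrated/not demonstrated and LAT complete/LAT incomplete and the associated 95% CIs will use standard statistical methods". AEs and treatment-plan impact are assigned to tables and listings there, and the Safety analysis section repeats for safety that "AE data will be summarised in tables and listings".

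Table 1 makes AE and serious AE (SAE) rates the safety endpoint. The Safety considerations section limits recording to events thought to be related to study procedures. The nearest figure to an expected rate is in the section on pleural staging by thoracoscopy, which cites for local anaesthetic thoracoscopy (LAT) in larger, symptomatic effusions "a low major complication rate (2.3% (95% CI 1.9% to 2.8" per cent).

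**The concern.** OPM prevalence does not enter the variance of an AE proportion under any interval method. An observed OPM rate of 8.3% is equally compatible with AEs in 2% or in 40% of participants, and the AE interval would differ greatly between the two.

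Reading the condition as applying to OPM alone does not rescue the sentence. The AE claim then becomes unconditional, and an unconditional ±10 points is untrue at n=50 over most of the range of possible rates.

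This is the article's only statement of what 50 patients can show about safety. The article itself says that the safety profile of LAT may differ in minimal effusions and has not been evaluated prospectively. A reader who relies on the sentence would believe that safety precision was settled by a low OPM rate.

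**Working it through.** **Inputs.** n=50, 95% confidence, a 10-point limit (read as a half-width) and OPM prevalence up to 15%, all from Sample size. The exact interval method is from Primary efficacy analysis. The 2.3% LAT major complication rate is from Pleural staging by thoracoscopy. The AE proportion is not stated, so a range is shown.

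**Step 1: reproduce the plan's figure.** By the normal approximation, n = 1.96² × p(1−p) / h², with h = 0.10.
- p = 0.15: 3.8415 × 0.1275 / 0.01 = 48.98, so 49. The stated 50 reproduces, and it is a calculation for the OPM proportion.
- p = 0.70 (the stated initial prevalence): 3.8415 × 0.21 / 0.01 = 80.67, so 81, not 96.
- p = 0.50: 3.8415 × 0.25 / 0.01 = 96.04, which matches 96. However 96 was derived, at that size the half-width was about 10.0 points or less for any proportion, including AEs. At 50 this no longer holds.

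**Step 2: where the promise holds at n=50, normal approximation.** Half-width = 1.96 × √(p(1−p)/50).
- 2.3%: 4.2 points
- 15%: 9.9
- 20%: 11.1
- 30%: 12.7
- 50%: 13.9

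Setting the half-width to 10 points gives p(1−p) = 0.01 × 50 / 3.8415 = 0.1302, so p = 15.4% or 84.6%. Between these values the limit is exceeded, whatever the OPM prevalence.

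**Step 3: the same under Clopper-Pearson, the method the plan names.**

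| Events / 50 | 95% CI | Half-width (points) |
|---|---|---|
| 0 | 0 to 7.1% | upper limit 7.1% |
| 6 | 4.5 to 24.3% | 9.9 |
| 7 | 5.8 to 26.7% | 10.5 |
| 10 | 10.0 to 33.7% | 11.8 |
| 15 | 17.9 to 44.6% | 13.4 |
| 25 | 35.5 to 64.5% | 14.5 |

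The limit is first passed at 7/50 (14%). By symmetry it stays passed up to 43/50. The 7/50 row also shows that the OPM statement itself, just below its 15% ceiling, is met by the normal approximation but not by the exact method.

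**Step 4: treatment-plan impact.** The same arithmetic applies to the proportion with a changed plan. That proportion is only partly driven by OPM. The Introduction argues that accurate staging would also encourage radical treatment in patients without OPM, so a negative thoracoscopy can change a plan too. Low OPM prevalence therefore does not imply few changed plans.

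**The case against.** The strongest reply is that the promise may well be met in practice. Only procedure-related events are recorded, and the one rate cited, 2.3%, gives ±4.2 points. The higher rates used above come from nowhere in the documents. That stands: the failure is conditional, not demonstrated. But 2.3% is a major complication rate for LAT in larger effusions. The endpoint here is all procedure-related AEs, including those from ultrasound and blood sampling, in a population whose safety profile is said to be possibly different. The documents give no ground for assuming a proportion below 14 to 15%.

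It can also be said that treatment-plan change depends on the OPM result, so conditioning on prevalence is less clearly wrong there. That is fair in part. OPM prevalence influences this proportion but does not fix it.

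Two stronger readings are tempting and are not supported.
- A reader might infer that no AE interval will ever be produced. Reporting in tables and listings does not exclude intervals within those tables, the article is condensed, and the SAP is not shown. What can be said is that the analysis sections name intervals for OPM and LAT completion and do not name the one that Sample size promises for AEs.
- A reader might infer that the trial would conclude equivalence to the 2.3% rate. No such comparison is planned and safety is descriptive. Zero events in 50, with an upper limit of 7.1%, lies within the 10-point promise and so does not contradict it. The 2.3% is also a LAT figure, while the trial permits video-assisted thoracoscopic surgery (VATS).

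**Conclusion.** The point holds as a misstatement of precision. The Sample size section makes ±10 points for the AE rate and treatment-plan impact follow from OPM prevalence of at most 15%, and it does not follow. At n=50 the claim is true for low proportions. It is false between about 15.4% and 84.6% by the normal approximation, or from 7/50 upward (to 43/50) by Clopper-Pearson, with a worst tabulated half-width of 14.5 points at 25/50.

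This rests on reading the 10% as a half-width, which is the reading that reproduces 50, and on a full denominator of 50. LAT-only rates will have a smaller denominator if some participants have VATS, and so wider intervals at the same proportion. The true AE and plan-change proportions are unknown, so how far the promise would be missed cannot be stated. The sample size, the conduct of the study and the primary analysis are unaffected.

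**What to change.** 1. In Sample size, limit the OPM-conditional statement to OPM prevalence.
2. State separately that precision for the AE and changed-plan proportions depends on their own values. Give Clopper-Pearson half-widths at n=50: 9.9 points at 6/50, 10.5 at 7/50, 11.8 at 10/50, 13.4 at 15/50 and 14.5 at 25/50, with an upper limit of 7.1% for 0/50. Using the planned method avoids quoting normal-approximation widths for exact intervals. Note that LAT-only rates will rest on fewer than 50 if VATS is used.
3. In Secondary efficacy analyses and Safety analysis, name Clopper-Pearson 95% intervals for the proportions of participants with at least one AE, with at least one SAE, and with a changed treatment plan. This matches the estimation that Sample size promises. If the SAP already specifies them, a cross-reference is enough.

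The cost is a few sentences and three intervals. The stated precision becomes less favourable, but nothing about recruitment or data collection changes.

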#### V.5.0, dated 16 November 2022

Removal of the MRI substudy, which involved perfusion MRI after registration and prior to thoracoscopy. Overall, 3/42 recruits had completed MRI by this time and these data will be reported in the results publication.Reduction of the sample size from 96 to 50. This was based on review of the OPM prevalence in the first 12 participants (see the Sample size section) and will allow the primary endpoint to be reported with the same precision as originally intended, but with a more realistic recruitment target.

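### The 10-point precision stated for 50 patients does not hold under the Clopper-Pearson interval that the plan specifies

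*Protocol article*

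**What the plan says.** Protocol article, Sample size: "The target sample size of 50 patients will allow estimation of the prevalence of OPM", together with the AE rate and the impact on treatment plans, "with 95% CI bounds not exceeding 10% if the OPM prevalence is ≤15" per cent. The method behind this figure is not named. The same section describes the earlier prevalence assumption as one "which was initially set at 70% (requiring a minimum sample size of 96"), and bases the new one on the first 12 recruits, "of whom only one case of OPM has been observed (8.3% OPM rate").

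Protocol article, Primary efficacy analysis: "The CI will be based on the Clopper-Pearson exact approach".

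Protocol article, V.5.0, dated 16 November 2022: the reduction from 96 to 50 "will allow the primary endpoint to be reported with the same precision as originally intended, but with a more realistic recruitment target".

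**The concern.** The primary result is one proportion with its 95% interval. The Sample size section concedes that the survival comparison no longer has its planned power, so the precision statement is the main quantitative support left for 50 patients. If it comes from a different interval from the one to be reported, readers will expect a narrower result than the analysis can give. The shortfall is on the upper side, and the upper bound shows how much occult pleural disease remains compatible with the data.

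The sentence also applies one condition, OPM prevalence of at most 15%, to three outcomes. The AE rate and the proportion of changed treatment plans have precision set by their own rates.

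**Working it through.** **Inputs.** n = 50, a 10-point limit, prevalence up to 15%, the earlier design of 96 at 70%, and the interim 1/12 = 8.3% (Sample size); Clopper-Pearson 95% interval (Primary efficacy analysis).

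**Step 1: reproduce the plan's figure.** The normal-approximation half-width is 1.96 × √(p(1−p)/n). At p = 0.15 and n = 50 it is 1.96 × √(0.15 × 0.85/50) = 0.0990, or 9.9 points. Solving for n at 10 points gives 1.96² × 0.15 × 0.85/0.10² = 49.0. So 50 fits this formula. A Wilson half-width would also fit (9.6 points at 7/50).

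**Step 2: apply the planned interval.** For x events in n patients, the lower limit is the 2.5% quantile of Beta(x, n−x+1) and the upper limit is the 97.5% quantile of Beta(x+1, n−x). At n = 50:

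| Events | Estimate | Exact 95% CI | Upper bound minus estimate (points) | Half-width (points) |
|---|---|---|---|---|
| 2 | 4% | 0.5-13.7% | 9.7 | 6.6 |
| 3 | 6% | 1.3-16.5% | 10.5 | 7.6 |
| 4 | 8% | 2.2-19.2% | 11.2 | 8.5 |
| 5 | 10% | 3.3-21.8% | 11.8 | 9.2 |
| 6 | 12% | 4.5-24.3% | 12.3 | 9.9 |
| 7 | 14% | 5.8-26.7% | 12.7 | 10.5 |

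At exactly 15% (x = 7.5, interpolated) the interval is 6.5-27.9%, with the upper bound 12.9 points above the estimate and a half-width of 10.7.

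- If the limit means the distance to each bound, it is met only at 0 to 2 events.
- If it means half-width, it is met up to 6 events and missed at 7, which is still inside the stated range.

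**Step 3: chance of meeting 10 points at n = 50.** With a binomial count, this is P(X ≤ 2) for both bounds and P(X ≤ 6) for half-width.

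| True prevalence | Half-width | Both bounds |
|---|---|---|
| 8.3% | 88% | 20% |
| 15% | 36% | 1.4% |

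**Step 4: sample size that would meet the claim at exactly 15% under Clopper-Pearson.** About 58 for half-width and 77 for both bounds (interpolated counts).

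**Step 5: compare with the earlier design.** Clopper-Pearson at 70% with n = 96 gives about 59.8-78.9%, a half-width of 9.6 with the farther bound 10.2 points away. At 15% with n = 50 the figures are 10.7 and 12.9.

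**Step 6: the other two outcomes.** The documents give no expected AE or plan-change rate. As an illustration only, assumed rates of 30% (15/50) and 50% (25/50) give exact upper bounds 14.6 and 14.5 points above the estimate, whatever the OPM prevalence.

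**The case against.** The wording is loose, and a half-width of 10 points is a fair reading. On that reading the exact interval meets the claim at every count up to 12%, and the chance of meeting it at the interim rate is 88%. The miss is about 0.5 to 0.7 points and arises only above 12%. The earlier design would itself fail the both-bounds reading (10.2 points), which suggests that half-width was meant. This stands and limits the size of the error. It does not remove it: 7/50 is inside the stated range and fails on either reading.

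The equal-precision statement can also be defended on its own terms. For 10 points, the normal approximation needs 96.0 patients at 50% and 81 at 70% (1.96² × 0.70 × 0.30/0.10² = 80.7). If 10 points was always the target, 50 patients at 15% match it by that method. The statement fails only under the exact interval, by about one point of half-width.

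A reader might infer more than the documents support:

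- That the figure is certainly a Wald calculation. No method is named, and Wilson also fits.
- That 96 was an error for 70%. Earlier versions also carried a survival power target, so the number may have had two drivers.
- That the condition of at most 15% is itself miscalculated. The exact interval for 1/12 is 0.2-38.5%, so the condition is uncertain, but the section states it as a condition and discloses the 1/12.
- That no intervals will be given for the AE rate and plan changes. Secondary efficacy analyses says "AE data and the impact on oncological treatment plans will be summarised in tables and listings", but this is a condensed article and such detail may sit in the analysis plan, which is not shown.

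**Conclusion.** Wrong as written. The stated precision for 50 patients does not follow from the interval that the plan fixes. For prevalence up to 15%, the exact half-width reaches about 11 points and the upper bound lies up to about 13 points above the estimate. The half-width shortfall is small; the clearer failure is the upper bound, which is 11 to 13 points above the estimate at 8% to 15%.

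The equal-precision statement in V.5.0 does not hold under the exact interval. Precision for the AE rate and the treatment-plan impact cannot be conditioned on OPM prevalence.

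A reader might conclude that the cut from 96 to 50 was unjustified. The documents do not support that: V.5.0 also cites a more achievable recruitment target, and the text introducing that amendment cites the need to report within the existing funding. The error is in the stated precision. The primary analysis is valid and the interval it reports will be correct.

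The result assumes all 50 patients are evaluable for the primary endpoint, and it uses interpolated counts where prevalence is set at exactly 15%.

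**What to change.** Keep 50 patients and the Clopper-Pearson interval.

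1. Replace the precision statement in Sample size with the exact limits, for example: with 50 evaluable patients the exact 95% CI is 2.2-19.2% if 4 have OPM and 5.8-26.7% if 7 do; for prevalence up to 15% the half-width is at most about 11 points and the upper bound at most about 13 points above the estimate.
2. In V.5.0, qualify or delete the claim that the reduced sample "will allow the primary endpoint to be reported with the same precision as originally intended", and let the recruitment and funding reasons stand.
3. Take the AE rate and treatment-plan impact out of the precision sentence, or state their precision at their own assumed rates.

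This changes wording in two sections and needs no extra patients. The only downside is that the stated precision becomes slightly less favourable.

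### Post hoc power is planned for an OS comparison expected to hold about 4 to 8 OPM-positive patients; it adds nothing to the confidence interval, and low prevalence alone would have defeated 80% power even at N=96

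*Protocol article*

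**What the plan says.** In the protocol article, the Sample size section lowers the planning prevalence of OPM from 70% to 15% or less, after one case in the first 12 participants (8.3%), and lowers the target from 96 to 50. It then says that this reduction in numbers costs the trial its "adequate power (80%) to detect an OS HR of 0.5 as planned in previous iterations of this protocol". The hazard ratio came from earlier retrospective data with "a median OS in OPM positive 6.32 months vs 12.65 months in OPM negative cases". The section continues "OS differences between OPM positive and OPM negative groups will nevertheless be reported" and closes with "Post hoc power calculations taking account of the observed prevalence will be performed".

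Under Secondary efficacy analyses, RFS and OS in the two groups are to be shown as Kaplan-Meier curves and "the HR will be estimated using Cox regression". Under Survival, OS is censored at 6 months for those still alive. No significance level is given for the OS comparison.

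**The concern.** Three stated choices fit poorly with the revised prevalence.

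- **Post hoc power.** Once the data are in, the confidence interval for the hazard ratio shows which effects remain compatible with them. A power figure for HR 0.5 at the realised split says less. It also invites the summary that no difference was found but the study was underpowered, in place of a statement of the range of effects.
- **Explanation of the lost power.** Only the cut in numbers is named. The change in group split is at least as damaging, and the section does not connect it to OS.
- **Ordinary Cox regression.** With two to four deaths in one group the partial likelihood is unstable. With none it has no finite maximum.

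What is at stake is how a secondary endpoint is read. The prevalence estimate and the safety reporting are unaffected.

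**Working it through.** **Inputs from the protocol article.** N = 96 and 50; prevalence 70%, 15% and 8.3%; HR 0.5; medians 6.32 and 12.65 months (ratio 0.4996); censoring at 6 months.

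**Assumed, because not stated.** Exponential survival, two-sided 5% (one-sided 5% as a range), and no loss to follow-up.

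**1. The plan's own figure.** Schoenfeld's formula for the deaths needed is d = (1.96 + 0.8416)² / [p(1−p)(ln 0.5)²]. At p = 0.70 this is 7.849 / (0.21 × 0.4805) = 77.8, so 78 deaths. Power is Φ(√[d·p(1−p)] × 0.6931 − 1.96). With N = 96 at 70% prevalence it is 79% at 18 months of follow-up and 83% at 24 months, so 80% is attainable. With the stated 6-month censoring (about 40 deaths) it is 52%. The original follow-up and significance level are not given, so the 80% cannot be confirmed exactly.

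**2. Change only the prevalence, keeping N = 96.**

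| Prevalence | OPM-positive | Deaths needed for 80% | Power if all 96 die (Schoenfeld) | Same, log-rank simulation |
|---|---|---|---|---|
| 15% | 14.4 | 7.849 / (0.1275 × 0.4805) = 128.1 | 68% | 68–69% (14 vs 82) |
| 8.3% | 8.0 | 7.849 / (0.0761 × 0.4805) = 214.6 | 47% | 51–52% (8 vs 88) |

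Both death counts exceed 96. With a one-sided 5% test the Schoenfeld maxima are 78% and 59%.

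**3. Change only N, keeping 70% prevalence.** N = 50 gives 31% at 6 months and at most 61% if all 50 die. The cut is therefore also sufficient by itself.

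**4. The trial as now planned, N = 50.** The chance of death by 6 months is 1 − 2^(−6/6.32) = 0.482 for OPM-positive and 1 − 2^(−6/12.65) = 0.280 for OPM-negative patients.

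| | 8.3% | 15% |
|---|---|---|
| OPM-positive patients | 4.2 | 7.5 |
| Deaths by 6 months, positive vs negative | 2.0 vs 12.8 | 3.6 vs 11.9 |
| Schoenfeld power, 6 months | 11% | 16% |
| Schoenfeld power, all die | 27% | 42% |
| Log-rank simulation, 6 months | 23–24% (4 vs 46) | 27% (7 or 8 positive) |
| Log-rank simulation, all die | 34–35% | 44–46% |

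Schoenfeld's approximation is rough at such an uneven split, so the simulation is the better guide. With all deaths observed, the simulated type I error is 8.4% for 4 vs 46 and about 7% for 7 or 8 positive, so part of the simulated power there is inflation.

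**5. Precision of the hazard ratio.** At 8.3%, SE(log HR) ≈ √(1/2.0 + 1/12.8) = 0.76, and exp(1.96 × 0.76) = 4.4. The 95% CI is then roughly the hazard ratio divided and multiplied by 4.4. At 15%, the SE is √(1/3.6 + 1/11.9) = 0.60 and the factor is 3.2.

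**6. Chance of no OPM-positive death by 6 months**, letting the number of OPM-positive patients vary: (1 − 0.083 × 0.482)^50 = 0.13 at 8.3%, and (1 − 0.15 × 0.482)^50 = 0.02 at 15%.

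**The case against.** The best defence is that the authors have been open. They declare the loss of OS power, report the prevalence change in the same paragraph, and promise an estimated hazard ratio, not a test. Four points in their favour stand.

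- A reader might infer that the sentence on the lost power is wrong. It is not: step 3 shows that the cut alone takes power below 80%. It names one of two sufficient causes.
- A reader might infer that the planned calculation is circular because power at the observed hazard ratio merely restates the p-value. The plan speaks of the observed prevalence, not the observed hazard ratio. The natural reading is HR 0.5 with the realised split, which is uninformative but not circular.
- One case in 12 has an exact 95% CI of 0.2% to 38.5%, so the final split is not known. At about 22% prevalence, N = 96 with every death observed would reach 80%. The statement about 96 participants therefore holds only within the plan's own range of 15% or less.
- Handling of sparse events is often left to an analysis plan, which is not shown, and Cox regression is a standard choice. Its absence from the article is not an omission. The point is that the estimator the article does name fits poorly with the counts its own prevalence implies.

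None of this gives the post hoc calculation a use that the confidence interval does not already serve.

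**Conclusion.** The point holds in limited form, as an inexpensive improvement to a secondary analysis. Post hoc power for HR 0.5 will be low throughout the plan's revised prevalence range: about 11% to 28% at 6 months, depending on prevalence and method, and below 50% even with complete follow-up. It tells the reader nothing beyond the confidence interval. The explanation of the lost power is true but incomplete, because at 15% prevalence or less 96 participants would have missed 80% as well. Ordinary Cox regression carries a 2% to 13% risk of no finite estimate at 6 months.

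These figures rest on exponential survival at the cited medians, a two-sided 5% test and a prevalence between 8.3% and 15%. The counts of about 4 patients and 2 deaths, and the 13%, belong to the 8.3% end only.

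**What to change.** In the Sample size section:

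- Delete the sentence on post hoc power.
- Keep the statement about the cut to 50, and add that at the revised prevalence of 15% or less neither 96 nor 50 participants would give 80% power for HR 0.5 (two-sided 5%).
- State that the OS comparison by OPM status is descriptive.

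Under Secondary efficacy analyses, report Kaplan-Meier estimates with 95% CIs per group, and a hazard ratio with 95% CI from a method suited to sparse events. Firth-penalised Cox regression with profile-likelihood limits is one reasonable choice.

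The cost is a few sentences and one option in standard software. Recruitment and the primary analysis do not change. The downside is that the OS comparison is openly labelled descriptive.
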